### Sample size calculation

In determining the appropriate group size in order to demonstrate a significant intervention effect on the primary endpoint, we used Cohen's effect size *d *to determine the difference between the patients' KATZ ADL index scores on the before and after measurement and divided by the SD of the difference scores of the control group as a benchmark for assessing the relative magnitude of ALDS score differences between both strategies. Although an effect size of 0.25 can be defined as small, such a difference in Katz ADL scores may be clinically important.

We have demonstrated that with a total of 506 patients (253 patients per treatment arm) we are able to statistically detect (power 80%, two-sided alpha of 5%) a minimal effect size on the Katz ADL index score. To allow for attrition due to mortality, which is expected to be 25% six months after admission, a total of 674 patients will be included in the trial.

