### Data analysis

Statistical analyses will be based on an intention-to-treat principle. Baseline assessments and outcome parameters will be summarized using simple descriptive statistics. The main analysis focuses on a comparison between the trial intervention and control group of the primary outcome, the Katz ADL index score. The same approach will be used with regard to the secondary outcome parameters, including survival rates. Survival data will be additionally analyzed using Kaplan-Meier survival curves and the log-rank test.

We will perform a predefined subgroup analysis for discharge destination (patients discharged to home versus nursing home). In all analyses statistical uncertainties will be quantified via corresponding 95% confidence intervals. Separate subgroup analysis will also be conducted on patients at intermediate (ISAR-HP score of two or three) and high risk for functional decline (ISAR-HP score of four or five). Finally, process outcome data will be analyzed qualitatively within the theoretical framework of the adaptive implementation model [23].

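### Separate analyses in the two ISAR-HP risk bands cannot show whether the effect differs by risk; the plan should name a comparison between the bands

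*Protocol article*

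**What the plan says.** The Data analysis section of the protocol article lists two subgroup factors. The first is discharge destination, worded as a contrast of home with nursing home. The second is baseline risk: "Separate subgroup analysis will also be conducted on patients at intermediate (ISAR-HP score of two or three) and high risk for functional decline", with scores four and five forming the high-risk band. Between the two, the section promises 95% confidence intervals throughout. It gives no test, model or decision rule for either factor, and no expected share of patients per risk band.

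The Sample size calculation section sizes the trial for the overall comparison only. On the effect it says "Although an effect size of 0.25 can be defined as small, such a difference in Katz ADL scores may be clinically important", and it then states that "with a total of 506 patients (253 patients per treatment arm) we are able to statistically detect" the minimal effect size with 80% power at a two-sided 5% level. After the mortality allowance, "a total of 674 patients will be included in the trial".

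**The concern.** The only purpose of splitting patients by risk is to learn whether the program works differently at different levels of risk. That question concerns the difference between two treatment effects. Two within-band results answer another question, namely whether there is evidence of an effect in each band alone. An interval for each band is not an interval for the difference between bands.

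The overall sample only just reaches its target power, so each band on its own falls short. When two underpowered comparisons are set side by side, chance alone will often make one significant and the other not, even if the effect is identical. If that pattern were read as a finding, it could support a wrong statement about who benefits. The Background counts aiming interventions at at-risk patients among the features of successful studies, so a reader may well look for such a statement.

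**Working it through.** **Inputs from the Sample size calculation section:** d = 0.25 (SD = 1 on the standardised scale), two-sided alpha 5%, power 80%, 253 per arm, 25% mortality. **Assumptions, not in the article:** the split of evaluable patients between the bands, the same true effect in both bands, and each band judged by its own p < 0.05.

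**Step 1: the plan's own figures.** n per arm = 2(1.960 + 0.842)² / 0.25² = 251.2, rounded up to 252. The t-test version gives 252.1, rounded up to the stated 253. With 253 per arm, power is 80.3%. For enrolment, 506 / 0.75 = 674.7 against the stated 674, a rounding difference. The plan's calculation reproduces.

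**Step 2: power within a band.** A band with fraction f of the patients has n = 253f per arm and SE = √(2/n). Power = Φ(d/SE − 1.960) + Φ(−d/SE − 1.960). At 50:50, n = 126.5, SE = 0.1257, d/SE = 1.988 and power is 51%.

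**Step 3: chance that exactly one band is significant.** The bands are independent, so with powers a and b the chance is a(1 − b) + b(1 − a). At d = 0.25 in both bands:

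| Split | Power, larger band | Power, smaller band | Exactly one significant |
|---|---|---|---|
| 50:50 | 51% | 51% | 50% |
| 60:40 | 59% | 43% | 51% |
| 70:30 | 65% | 34% | 55% |
| 80:20 | 71% | 24% | 61% |

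At 80:20, for example: 0.711 × 0.758 + 0.242 × 0.289 = 0.609.

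**Step 4: sensitivity to the true uniform effect** (splits 50:50 to 80:20):

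| True d in both bands | Exactly one significant |
|---|---|
| 0 | 9.5% (2 × 0.05 × 0.95) |
| 0.10 | 22% |
| 0.15 | 35–37% |
| 0.20 | 46–51% |
| 0.25 | 50–61% |
| 0.30 | 45–62% |
| 0.35 | 33–57% |

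**Step 5: the interaction test.** The statistic is the difference of the two band estimates divided by √(SE₁² + SE₂²). In one million simulated trials per split, with a uniform effect of 0.25, it was falsely significant in 4.96% to 5.01%. Exactly one band significant together with a significant interaction occurred in 4.2% to 4.8%. Among trials with a significant overall result, exactly one band was significant in 57% (50:50) to 71% (80:20).

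**Step 6: what the interaction test can detect.** At 50:50, the SE of the difference is √(4/126.5) = 0.178. A difference in d of (1.960 + 0.842) × 0.178 = 0.50 is needed for 80% power, twice the design effect.

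**The case against.** The strongest reply is that the article is nearly silent here. It does not name even the test for the primary outcome. Whether subgroup effects are compared through an interaction term is ordinary material for an analysis plan, which is not shown. The word for separateness may partly mean a further subgroup analysis after the one on discharge destination. A reader might infer that the sponsor chose separate tests instead of an interaction test. The text does not support that: it does not mention an interaction test, and it does not exclude one.

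A second reply is that the harm needs a rule the article does not contain. Nowhere does it say that each band will be judged by its own significance, or that a significant and a non-significant band will be read as a difference. It promises confidence intervals, and band estimates with intervals are legitimate description.

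A third is that the two bands are fixed in advance, which is a strength. Replacing them with a linear trend over scores 2 to 5 brings its own assumption. Table 1 gives the walking-device item two points and the other items one, so equal steps in effect are not self-evident.

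All three stand as limits on the point. They do not remove it. The most natural reading of the sentence is an analysis within each band. That wording fixes a form of analysis that leaves the question unanswered, and the promised intervals do not fill the gap unless one of them is for the difference.

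**Conclusion.** The point holds in a limited form. The article plans separate analyses in the ISAR-HP 2–3 and 4–5 bands and names no comparison between them. Separate band results do not show whether the effect differs by risk.

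The figure of 50% to 61% against 5% is conditional. It rests on a uniform true effect equal to the trial's design value, on 506 evaluable patients, on an assumed split between 50:50 and 80:20, and on reading each band by its own p < 0.05. A reader might conclude that a false finding of benefit in one band only is about as likely as not whatever the truth. The documents do not support that: the chance is about 22% at a uniform d = 0.10 and about 10% with no effect at all.

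The matter concerns a secondary subgroup analysis. The primary comparison, the sample size and the conduct of the trial are untouched.

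**What to change.** State in the analysis text that the subgroup question will be answered by one model on all patients with treatment, ISAR-HP band (2–3 versus 4–5) and their interaction. Base any statement on differing effects on the interaction estimate and its 95% CI. Present the two band estimates with their intervals as description, without separate significance claims. An interaction with the ISAR-HP score as a trend may be added as an optional sensitivity analysis; the prespecified bands need not be given up.

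The change is to wording only and needs no further patients or data. The real cost is that the interaction test has low power, so a subgroup claim becomes harder to make. That reflects what a sample sized for the overall effect can support.

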## Discussion

With an ageing population in many countries and increasing life expectancy, there is an urgent need to improve outcomes of hospital admission. Preservation of decline in ADL functions and preventing institutionalization have become a more important focus of care, rather than only minimizing mortality rates. Several approaches to improve hospital outcomes have been studied focusing on comprehensive geriatric assessment and intensive home follow up after discharge. The present RCT combines these approaches to provide optimal care during hospital admission and to improve ADL functioning after discharge.

The study is conducted as part of the National Care for the Elderly program in which special emphasis is given to regional geriatric care networks. The current study will provide information on the feasibility of the intervention, collaboration between hospitals and primary care as well as on structural funding of care.

## Abbreviations

(ADL): activities of daily living; (ALDS): AMC linear disability scale; (ISAR-HP): Identification of Seniors at Risk-Hospitalized Patient; (CGA): comprehensive geriatric assessment; (CN): community care nurse; (CNS): clinical nurse specialist in geriatrics; (DEFENCE): Develop strategies Enabling Frail Elders New Complications to Evade; (EQ-6D) Six-Dimensional EuroQol instrument; (ES): effect size; (GEM): Geriatric Evaluation and Management units; (GP): general practitioner; (IADL): Instrumental Activities of Daily living; (IQCODE): informant questionnaire on cognitive decline in the elderly; (MMSE): Minimal Mental State Examination; (RCT): randomised clinical trial; (RN): registered nurse; (NHP): nursing home physician; (SD): standard deviation.

